#### Secondary Outcomes

Pain unpleasantness, pain interference, muscle tension, anxiety, and vital signs will also be assessed in relation to each intervention, and means and standard deviations will be reported and used for data analysis.

### Instrumentation

#### Pain Intensity

The NRS will be used to assess pain intensity. The NRS is an 11-point unidimensional self-report scale recommended for the assessment of pain intensity where 0 is no pain and 10 the worst possible pain. Details about the NRS and other assessment tools are summarized in Table 2.

**Table 2 table2:** Description and psychometrics of the instruments used for outcome data collection.

Outcome	Instrument	Scoring	Psychometrics	
			Reliability	Validity
Pain intensity	NRS^a^ (0-10)	0: no pain, 10: worst possible pain	High test-retest reliability observed in cancer patients when measuring pain exacerbations (kappa=.86) and background pain (kappa=.80) [48].	High concurrent validation with the Visual Analog Scale (*r*=.84 to .94, *P*<.001) [2,49]). Good discriminatory capability between background and peak intensity pain in the oncology population with only 14% of the 240 patients giving inconsistent evaluations [48].
Pain unpleasantness	NRS (0-10)	0: not at all unpleasant, 10: most unpleasant feeling possible		Good convergent validation with the Facial Affective Scale (*r*=.71, *P*<.01). Discriminant validation: correlated with the Functional Disability Inventory (*r*=.28, *P*<.05). Good sensitivity to change over a 2-week period (mean change 1.89, *t*_68_=5.30, *P*<.001) in children and adolescents after surgery [50].
Pain interference	Adapted BPI^b^: pain intensity index (4 NRS 0-10 subscales), pain interference index (7 NRS 0-10 subscales)	Pain intensity: 0: no pain, 10: pain as bad as you can imagine Pain interference: 0: no interference, 10: interferes completely	Internal consistency was also supported for this patient population with Cronbach alpha coefficients .84-.89 for the severity scale and .91-.94 for the interference scale.	Factor analysis revealed two distinct factors (ie, pain intensity and interference) accounting for 66% and 75% of total variance, respectively [51]. Scores on both scales declined significantly from baseline to follow-up, thus testifying to the responsiveness of the BPI for detecting changes [51].
Muscle tension	CPOT^c^ muscle tension subscale (0-2)	0: no resistance, 1: resistance, 2: strong resistance	Moderate to high interrater reliability of CPOT scores between trained raters with intraclass correlation of 0.30-0.86 [52] and kappa of 0.52-0.88 [53,54].	Discriminant validation: significant increases in CPOT scores during painful compared to nonpainful procedures [52-55]. Criterion validation: moderate correlation with patient self-report of pain intensity (*r*=.40-.69, *P*<.05) [52,53]. Convergent validation: moderate correlation with pain unpleasantness (*r*=.31, *P*<.01) [52]. Sensitivity of 86% and a specificity of 78% for the presence of pain during turning procedures were shown for a CPOT cut-off score >2 [56].
Anxiety	NRS (0-10)	0: no anxiety, 10: worst possible anxiety	Individual validity and reliability tests were not conducted to date with the NRS for anxiety, but it has been included in the Edmonton Symptom Assessment System, whose validity and reliability have received support over the past two decades [57].			

^a^NRS: Numeric Rating Scale

^b^BPI: Brief Pain inventory

^c^CPOT: Critical-Care Pain Observation Tool

#### Pain Unpleasantness

The NRS will be used to assess the pain unpleasantness of patients. The unpleasantness dimension of symptom experience refers to the degree to which the person is bothered by the unpleasant symptom [58]. The pain unpleasantness NRS is scored on a scale from 0 to 10 with the anchors “not at all unpleasant” for 0 and “most unpleasant feeling possible” for 10.

#### Pain Interference

An adapted version of the Brief Pain Inventory (BPI) will be used. The BPI is a short pain assessment scale developed to measure the intensity of pain during the last 24 hours (sensory dimension) and the interference of the pain in the patient’s life (cognitive dimension) [59,60]. The pain severity items are rated individually on an NRS with 0 assigned to “no pain” and 10 to “worst possible pain.” Patients are asked to rate their pain severity at the time of interview (pain now) and the worst pain, the least pain, and average pain during the last 24 hours. The 7 items of pain interference evaluate the impact of pain on general activity, mood, walking/mobilization, work, relationships, sleep, and enjoyment of life. The item work is not considered relevant in the context of cardiac surgery patients who are hospitalized in the ICU or acute care units and will not be administered. Instead, additional items about coughing, deep breathing, appetite, and concentration will be included; these have been observed to have moderate-to-severe pain interference in postoperative cardiac surgery patients [4,15,61].

#### Muscle Tension

The assessment of muscle tension will be based on an ordinal scale derived from the behavioral pain scale Critical-Care Pain Observation Tool (CPOT), which was developed and tested for the assessment of pain in critically ill patients after cardiac surgery [53]. Evaluation of muscle tension is done by performing passive flexion and extension of the upper limbs of patients at rest with a score of 0 being assigned for “no resistance to passive movements,” 1 for “resistance to passive movements,” and 2 for “strong resistance to passive movements or incapacity to complete them.”

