### Data Collection

Sociodemographic (eg, age, gender) and medical-surgical data (eg, type of cardiac surgery, analgesia) will be collected using standardized data collection sheets. Prior to the delivery of each intervention (hand massage or hand-holding) and before the first data collection for the standard care group, patients will complete a self-administered data collection sheet with 5 short questions using the NRS for the self-report of pain intensity, pain unpleasantness, and anxiety, a body map for identifying the site of pain, and an open-ended question for a description of the quality of pain. The interventionist will be masked to patients’ self-reports, which will be accessed only at the end of data collection to verify for missing data. The form will be completed before, immediately after the intervention (hand massage or hand-holding), and 30 minutes later, for a total of 3 data collection points per intervention. Those assigned to standard care will complete the form at similar times. This bundle of assessments will be repeated for each of the 3 interventions. Muscle tension and vital signs will also be evaluated at the same assessment points.

Finally, pain interference will be evaluated using a structured interview using the BPI on the second postoperative day to examine any carry-over effects.

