### Data Analysis

The data will be entered in the SPSS software version 22.0 (IBM Corp), and a random subset of data will be used to identify missing or erroneous values. This study aims to use intention-to-treat analysis by including every participant who has been randomized, regardless of group assignment, study withdrawal, or protocol deviations.

Descriptive statistics will be calculated for sociodemographic and medical-surgical data and the baseline scores on all the outcome variables. Group differentiation in sociodemographic and medical-surgical characteristics for participant patients will be investigated using chi-square tests of independence for nominal level variables and one-way analyses of variance (ANOVA) for interval and ratio level variables. If group differences exist, the respective variable will be included as a covariate in the subsequent analyses. Frequencies and percentages of the location and descriptors of pain (ie, sensory dimension of pain) will be calculated for each group and assessment point and used to describe the pain characteristics of participants. Data on pain location and quality will be compared over time.

Repeated measures between ANOVA factors will be used to test for treatment (hand massage, hand-holding, rest), time (before, immediately after, and 30 minutes later), and interaction effect for pain intensity, pain unpleasantness, muscle tension, anxiety, and means of vital signs. This will be run for each intervention and each of these outcome variables. One ANOVA test will be performed for pain interference with the independent variable being group assignment (hand massage, hand-holding, standard care). The main comparison of interest is between the hand massage and standard care group and the difference in means pre- and immediately posttreatment.

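### Muscle tension, a three-level ordinal score with a floor at 0, is tested by unadjusted pre-to-post difference in means: valid, but inefficient for this secondary outcome

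*Protocol article*

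**What the plan says.** The Muscle Tension section under Instrumentation states "The assessment of muscle tension will be based on an ordinal scale". Table 2 lists three levels: "0: no resistance, 1: resistance, 2: strong resistance". The rating is made on passive movement of the upper limbs with the patient resting, and 0 is the lowest possible score.

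Under Secondary Outcomes, where muscle tension is named, "means and standard deviations will be reported and used for data analysis". Data Analysis lists it among the outcomes for repeated-measures ANOVA, which tests treatment, time and "interaction effect for pain intensity, pain unpleasantness, muscle tension, anxiety, and means of vital signs", run separately for each of the three sessions. It adds: "The main comparison of interest is between the hand massage and standard care group and the difference in means pre- and immediately posttreatment".

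Data Collection gives the timing: "Muscle tension and vital signs will also be evaluated at the same assessment points", that is, before, immediately after and 30 minutes after each session.

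Data Analysis provides for covariates only where the arms differ on sociodemographic or medical-surgical characteristics. The pre-session muscle score is not named as one. The eligibility criteria set no minimum tension.

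**The concern.** A patient who scores 0 before a session cannot show relaxation. The change is then zero or a worsening, whichever arm the patient is in. Nothing at entry keeps such patients out, and the floor applies afresh at each of the three sessions. A simple pre-to-post difference carries the noise of the pre-session score in full, and on a floored score it dilutes the contrast between arms further. A mean and SD of a 0/1/2 code also hide what a reader wants to know: how many patients moved from resistance to none.

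Muscle tension is one of the outcomes in the stated objective. If most patients start at 0, a null result under this plan would be hard to tell apart from a floor effect.

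**Working it through.** **The plan's own figure.** The article gives no power for muscle tension; its sample size rests on pain intensity alone. The stated minimum of 72 can be reproduced under two assumptions of mine: evenly spaced arm means (0, 0.75, 1.5) and a correlation of 0.5 between the three measurements.
- Variance of arm means = (0.75² + 0² + 0.75²)/3 = 0.375, and f² = 0.375/2.0² = 0.09375 (f = 0.306).
- λ = N·f²·m/(1 + (m−1)ρ) = 72 × 0.09375 × 3/2 = 10.125, on 2 and 69 df. Power is 0.802.
- 72 × 1.1 = 79.2, in line with the stated 79.
- 72/3 = 24 evaluable patients per arm, used below.

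**Set-up for muscle tension.** Each patient has a latent pre- and post-session tension, bivariate normal with unit variances and correlation 0.5. The score is 0 up to c₁, 1 between c₁ and c₂, and 2 above c₂, where c₁ = Φ⁻¹(p₀) and c₂ = Φ⁻¹(p₀ + p₁). Massage lowers the latent post-session value by δ = 0.9 SD; rest leaves it unchanged. The comparison is massage against rest, immediately after a session, at two-sided 5%. The shares p₀ and p₁, the shift and the correlation are all assumptions.

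**Power by share of patients at 0 before the session**

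| Analysis | 80% | 60% | 40% | 20% |
|---|---|---|---|---|
| t test on change | 0.23 | 0.40 | 0.57 | 0.70 |
| Wilcoxon on change | 0.22 | 0.38 | 0.54 | 0.69 |
| Linear ANCOVA on the 0–2 score | 0.41 | 0.66 | 0.78 | 0.84 |
| Rank ANCOVA | 0.43 | 0.66 | 0.77 | 0.84 |
| Proportional odds, baseline-adjusted | 0.55 | 0.71 | 0.80 | 0.87 |

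A separate run, with the remaining patients split 15/5, 30/10, 40/20 and 50/30 between scores 1 and 2, agrees to within 0.03: change test 0.22, 0.41, 0.57, 0.67; linear ANCOVA 0.39, 0.67, 0.79, 0.83. In that run the full three-arm, three-time interaction test, with hand-holding given half the shift, had power 0.18, 0.33, 0.51 and 0.60. At a smaller shift of 0.6 SD the change test had 0.15, 0.26, 0.36 and 0.38, and linear ANCOVA 0.24, 0.39, 0.48 and 0.50.

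**Where the loss comes from**
- *Means or ranks, same contrast.* On change, t minus Wilcoxon is 0.01, 0.02, 0.03 and 0.01. In ANCOVA, rank minus linear is 0.02, 0.00, −0.01 and 0.00. This is negligible.
- *Adjusting for the pre-session score, still on means.* 0.41 − 0.23 = 0.18; 0.66 − 0.40 = 0.26; 0.78 − 0.57 = 0.21; 0.84 − 0.70 = 0.14.
- *Proportional odds over linear ANCOVA.* 0.14, 0.05, 0.02 and 0.03. It matters mainly when most patients are at the floor.
- *The scale itself.* For an uncategorised, unfloored measure, the SD of change is √(2(1 − 0.5)) = 1 and the standard error of the difference is √(2/24) = 0.289. The standardised effect is 0.9/0.289 = 3.1, and the change test would have power 0.88.

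**Type I error.** With no shift, rejection was 0.050 to 0.054 for the change test and 0.048 to 0.060 for the repeated-measures interaction (2,000 runs). The proportional-odds likelihood-ratio test gave 0.058, 0.030 and 0.078 at 80, 60 and 40% (400 runs, Monte Carlo standard error √(0.05 × 0.95/400) = 0.011), so it may be slightly liberal at this size.

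**The case against.** The strongest reply is that the ordinal scale is not the cause. A reader might infer that taking means of an ordinal code throws away the power, or that unequal intervals and variances invalidate the ANOVA. Neither is supported: ranks on the same contrast do no better, and the planned test holds its level. That reply stands.

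It also stands that the floor belongs to the instrument. A patient at 0 cannot relax further under any model.

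The size of the loss depends on shares and a shift that the article does not give. With only 20% at 0 the change test already reaches 0.70, so a claim that a real effect will probably be missed goes beyond the documents. Nor can muscle relaxation be called the trial's claimed mechanism: the Theoretical Framework does not name it, although the Background cites muscle relaxant effects in the pilot trial.

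Proportional odds has its own weakness. With 5% in the top category, 24 × 0.05 = 1.2 patients per arm are expected there.

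Finally, an unseen analysis plan could add the covariate. But this is not a silence in the article: it names the method and the contrast for this outcome. What survives is that adjustment for the pre-session score raised power at every floor share tried, using data already being collected.

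**Conclusion.** The point holds as one of efficiency and presentation. The article fixes an unadjusted pre-to-post difference in means for a score it calls ordinal, with three levels and a floor. The test is valid. Under the assumptions above (24 per arm, correlation 0.5, shift 0.9 SD), moving to a baseline-adjusted ordinal model raises power over the change test by 0.32, 0.31, 0.23 and 0.17 as the share at 0 falls from 80 to 20%. Most of that gain comes from the adjustment, and it shrinks in absolute terms at a shift of 0.6 SD. The exact size cannot be fixed from the document. The matter concerns one secondary outcome, and the conclusions on pain intensity do not depend on it.

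**What to change.** For muscle tension, replace the pre-to-post ANOVA contrast by a model of the score immediately after each session, with arm and the pre-session category as terms. Use proportional odds, or a rank test stratified by pre-session category if categories are sparse, with the switching rule written down before the data are seen. Keep massage against standard care as the main contrast. Report counts of 0, 1 and 2 by arm and time, alongside or instead of means and SDs, and state how many patients were at 0 before each session and so could not improve.

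The cost is one line of analysis wording and one table, with no new data and no change to the sample size. The downside is that an odds ratio replaces a mean difference. If a mean difference is preferred, linear ANCOVA on the 0–2 score keeps it and still recovers most of the gain, though noticeably less when most patients start at 0.

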#### Anxiety

For consistency and because intensity of anxiety is of interest in this study, the NRS will also be used to assess patients’ anxiety levels.

#### Vital Signs

Means of blood pressure (ie, systolic, diastolic, mean arterial pressure) and heart and respiratory rates will be collected from the ICU bedside monitors for 1 minute at each assessment point.

### Data Collection

Sociodemographic (eg, age, gender) and medical-surgical data (eg, type of cardiac surgery, analgesia) will be collected using standardized data collection sheets. Prior to the delivery of each intervention (hand massage or hand-holding) and before the first data collection for the standard care group, patients will complete a self-administered data collection sheet with 5 short questions using the NRS for the self-report of pain intensity, pain unpleasantness, and anxiety, a body map for identifying the site of pain, and an open-ended question for a description of the quality of pain. The interventionist will be masked to patients’ self-reports, which will be accessed only at the end of data collection to verify for missing data. The form will be completed before, immediately after the intervention (hand massage or hand-holding), and 30 minutes later, for a total of 3 data collection points per intervention. Those assigned to standard care will complete the form at similar times. This bundle of assessments will be repeated for each of the 3 interventions. Muscle tension and vital signs will also be evaluated at the same assessment points.

Finally, pain interference will be evaluated using a structured interview using the BPI on the second postoperative day to examine any carry-over effects.

### Data Analysis

The data will be entered in the SPSS software version 22.0 (IBM Corp), and a random subset of data will be used to identify missing or erroneous values. This study aims to use intention-to-treat analysis by including every participant who has been randomized, regardless of group assignment, study withdrawal, or protocol deviations.

Descriptive statistics will be calculated for sociodemographic and medical-surgical data and the baseline scores on all the outcome variables. Group differentiation in sociodemographic and medical-surgical characteristics for participant patients will be investigated using chi-square tests of independence for nominal level variables and one-way analyses of variance (ANOVA) for interval and ratio level variables. If group differences exist, the respective variable will be included as a covariate in the subsequent analyses. Frequencies and percentages of the location and descriptors of pain (ie, sensory dimension of pain) will be calculated for each group and assessment point and used to describe the pain characteristics of participants. Data on pain location and quality will be compared over time.

Repeated measures between ANOVA factors will be used to test for treatment (hand massage, hand-holding, rest), time (before, immediately after, and 30 minutes later), and interaction effect for pain intensity, pain unpleasantness, muscle tension, anxiety, and means of vital signs. This will be run for each intervention and each of these outcome variables. One ANOVA test will be performed for pain interference with the independent variable being group assignment (hand massage, hand-holding, standard care). The main comparison of interest is between the hand massage and standard care group and the difference in means pre- and immediately posttreatment.

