### Sample Size and Sampling Procedure

A power analysis was conducted using the G*Power 3 program [38] to estimate the sample size required to capture the potential effects of massage to decrease the primary outcome (pain intensity) and to strengthen the statistical conclusion validity. The mean treatment difference was observed to be greater than 1.5 in several RCTs [11,26,39,40] and approximates the clinically significant difference of 2 points on the 0 to 10 Numeric Rating Scale (NRS) [41]. This trial is powered to be able to detect a difference in the pain intensity score of 1.5 between the hand massage and standard care group. The standard deviation of pain intensity scores is approximately a 2.0 value, which was selected for the sample size calculation. To detect a mean difference in pain intensity scores of 1.5 points (SD 2.0) immediately after the third massage with a 2-sided significance level of .05 and power of .80 with equal allocation to 3 arms and a repeated measures between factors context with 3 measurements would require a minimum of 72 patients.

Given the low attrition rates observed with this patient population (0% [9,10,30] and 35/287 (12.2%) [29]), a 10% drop-out rate is considered in the calculation of the total sample size. Therefore, the final size required for this RCT is 79, and it will be reached using convenience sampling.

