## Discussion

### Interpretation

Pain is one of the most common and severe symptoms cardiac surgery patients experience during their ICU stay. The adverse effects of unrelieved acute postoperative pain are numerous and can be taxing to cardiac surgery patients during their recovery but worryingly also on the long term. There is a general agreement in practice guidelines that multimodal approaches to pain management should be implemented in the ICU [20]. Massage, a complementary nonpharmacological intervention, could play an important role in enhancing pharmacological analgesia and maximizing pain relief in the cardiac surgery patients, and providing rigorous empirical evidence for its use in the ICU is strongly awaited to inform practice guidelines.

In the proposed RCT, eligible and consenting patients will be randomly assigned to either the massage (ie, experimental), hand-holding (ie, active control) or standard care group (ie, passive control). While the administration of pleasant and potentially beneficial interventions [42] can help minimize attrition rates in the experimental and active control groups, the use of standard care with rest only could cause higher withdrawals in this group and subsequently increase the risk of attrition bias. In order to counter such bias and as an incentive to make participation in the study more attractive, patients will be informed that hand massage can be offered to those assigned to the active or passive control groups at the end of data collection, if desired.

A strength of this RCT is the administration of massage in the actual ICU environment and the clinical context of the first 24 hours post–cardiac surgery when monitoring is accrued, thus enabling an evaluation of the effectiveness of this intervention on the patient’s pain and related signs and symptoms. However, the same ICU environment could interfere with the delivery of some of the planned hand massages and hand-holding in the selected mode (eg, quiet environment) and dose (ie, 3 times for 20 minutes). In order to monitor these interferences and consider them in the interpretation of study findings, a camera will be used to videorecord the interventions. Nonetheless, even if these interventions can no longer be administered (eg, use of invasive equipment on hands postrandomization), attempts to continue collecting patients’ self-reports of symptoms will be prioritized over imputation for missing data.

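### Intention-to-treat is promised for every randomised patient, but the named repeated-measures ANOVA excludes anyone missing one of a session's three scores

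*Protocol article*

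**What the plan says.** In the protocol article, Data Analysis sets the population: "This study aims to use intention-to-treat analysis by including every participant who has been randomized, regardless of group assignment, study withdrawal, or protocol deviations". It then sets the method: "Repeated measures between ANOVA factors will be used to test for treatment (hand massage, hand-holding, rest), time (before, immediately after, and 30 minutes later", with an interaction term, and adds "This will be run for each intervention and each of these outcome variables". Data Collection confirms three scores per model: "for a total of 3 data collection points per intervention". On software, "The data will be entered in the SPSS software version 22.0 (IBM Corp"). The main comparison is hand massage versus standard care in the difference between the pre-treatment and immediately post-treatment means.

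Four other places bear on missing scores:

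- Sample Size and Sampling Procedure: "a 10% drop-out rate is considered in the calculation of the total sample size", taking 72 to 79. The target is set at session 3: "To detect a mean difference in pain intensity scores of 1.5 points (SD 2.0) immediately after the third massage".
- Discussion, Interpretation: "the use of standard care with rest only could cause higher withdrawals in this group", with attrition bias named as the consequence. As a counter-measure, control patients may be offered massage after data collection.
- The same section ranks continued collection of self-reports above imputation. It names no imputation method.
- Criteria for Modifying Interventions: consenting patients stay in data collection where possible after the intervention is stopped.

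**The concern.** Classical repeated-measures ANOVA, including the SPSS repeated-measures procedure, needs a value at every level of the time factor and deletes a patient who lacks one. Once any score is missing, the named method and the named population cannot both hold. What the article describes is then a complete-case analysis under an intention-to-treat label.

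Two features make this more than a labelling matter. The main comparison needs two scores, yet the three-level model also discards a patient who has both but did not complete the 30-minute form. And the arm in which the article foresees possible extra withdrawal is one of the two arms in the main comparison. If the patients who leave differ in their change in pain, the groups compared are no longer those that randomisation formed.

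**Working it through.** **Inputs from the article:** difference 1.5 points, SD 2.0, two-sided alpha .05, power .80, 3 arms, 3 measurements, N = 72 rising to 79, drop-out 10%, attrition in earlier studies 0% to 12.2%. **Assumed, because not stated:** correlation between measurements rho = 0.5, and equally spaced arm means.

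**1. The plan's own figure.**
- Arm means 0, 0.75 and 1.5 have standard deviation √[(0.75² + 0 + 0.75²)/3] = 0.612, so f = 0.612/2.0 = 0.306.
- For the between-factors test, λ = f²·N·m/[1 + (m − 1)rho] = 0.09375 × 72 × 3/2 = 10.1 on 2 and 69 degrees of freedom.
- Power is 0.8025, so 72 reproduces. With rho from 0.3 to 0.7, the required N runs from 60 to 87.
- 72 × 1.1 = 79.2, which gives the stated 79.

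**2. Who enters the session-3 model.**
- At 10% drop-out by session 3: 79 × 0.10 = 7.9 excluded and 79 × 0.90 = 71.1 analysed. Power is 0.797.
- At 12.2%: 79 × 0.878 = 69.4 analysed. Power is 0.786.

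**3. Missed forms on top of drop-out.** No rate is given, so this is a range. If each form is missed independently with probability q, the number analysed is 79 × 0.90 × (1 − q)³.

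| q | analysed | power |
|---|---|---|
| 0% | 71.1 | 0.797 |
| 2% | 66.9 | 0.77 |
| 5% | 61.0 | 0.73 |
| 10% | 51.8 | 0.65 |

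At q = 5%, 1 − 0.95³ = 14% of remaining patients are lost from a session. Of these, 0.95² × 0.05 = 4.5% (about 3 of 71) have both scores for the main comparison and lack only the 30-minute form. A session's three forms are filled in close together, so misses would probably cluster and the true loss be smaller.

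**4. Possible bias, illustration only.** Assume no true effect, SD 2, rho 0.5 and no loss in the massage arm. In the rest arm, the fraction d with the highest value of post-session pain plus independent noise (SD 2) leaves.
- The covariance of change with that driver is 4 − 2 = 2, and the driver's SD is √8 = 2.83.
- The completers' mean change therefore falls by (2/2.83) × φ(z)/(1 − d), where z is the 1 − d normal quantile.
- At d = 12.2%: 0.707 × 0.202/0.878 = 0.16 points. Simulation gave 0.158.
- Simulation gave 0.25 at d = 20% and 0.35 at d = 30%. With equal 10% loss in both arms it gave about zero.
- Against the 1.5-point target, 0.16 is 0.16/1.5 = 11%.

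The rest arm appears to improve more than it did, so under this mechanism the shift works against massage.

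**The case against.** The strongest reply is that the article mentions imputation. ANOVA on imputed data could include every randomised patient, and an article may leave the imputation method to a fuller document. That limits the claim: a complete-case result follows from the text as written, but it is not declared. It does not remove the point. The conflict lies between two things the article does fix, and imputation appears only as ranking below continued collection.

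Several stronger readings are tempting and are not supported:

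- **That drop-out is expected to differ by arm.** The article says rest could cause more withdrawals and plans a counter-measure. It also keeps patients in data collection after the intervention stops. This is a named risk, not a forecast.
- **That the result will favour massage.** The direction depends on who leaves. The illustration above goes the other way. If leavers have equally more pain before and after a session, a raw mean is biased but the change score, the planned metric, is not.
- **That the trial loses its power.** The 79 already allows for 10% drop-out, and each session has its own model, so a missed form costs only that session.
- **That patients will be analysed by treatment received.** The words about group assignment in the intention-to-treat sentence are loose. But the same section uses group assignment as the independent variable for pain interference, which points to analysis by assigned arm.

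**Conclusion.** The point holds as an internal conflict: the named ANOVA cannot include every randomised participant once a score is missing, and no named method fills the gap. At the plan's own 10% drop-out, about 8 of 79 patients would be absent from the session-3 analysis on which the trial is powered. That figure assumes the drop-outs have left by session 3.

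The power loss at that rate is negligible (0.797 against the planned 0.80, rho 0.5 assumed). The harm is to the randomised comparison and to the accuracy of the intention-to-treat claim. Any bias is of unknown size and direction. The 0.16 points rest on one-sided, pain-related drop-out at the highest rate the article cites.

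**What to change.** Replace the repeated-measures ANOVA with a likelihood-based linear mixed model (SPSS MIXED, REML, unstructured covariance) with arm, time and arm-by-time, using all observed scores.

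- **Keep the pre-intervention score as a response, not a covariate.** As a covariate, a patient with no later score would still drop out of the model.
- **Model the three sessions together where possible.** A patient who leaves before session 3 has no score in a session-3-only model and informs it only through earlier sessions. Nine assessments give 9 × 10/2 = 45 covariance parameters, so name a simpler fallback structure in advance. A patient with no score at all contributes under neither form; report the number.
- **Keep the plan's own contrast:** massage versus standard care in change from before to immediately after treatment, for each session including session 3.
- **Reword the intention-to-treat sentence** so that patients are analysed in the group to which they were randomised, with all available scores.
- **Add one sensitivity analysis** that shifts missing scores by arm. The mixed model relies on missingness being explained by observed scores and would not by itself remove drop-out driven by an unobserved score.

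The cost is slightly more analysis work. Sample size, forms and schedule do not change, and SPSS is already named. The Results section reports 24 patients randomised so far, so the change can be made well before analysis.
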